### Interventions

#### Inulin group.

Participants in the inulin group will consume Inulia® IQ (inulin, 4 g per sachet), taken twice daily (8 g/day total) for 4 weeks.

#### Placebo group.

Participants in the placebo group will consume maltose powder identical in appearance (4 g per sachet), taken twice daily (8 g/day total) for 4 weeks.

#### Product matching.

Both the inulin and placebo products are white, odourless powders supplied in identical sachets labelled only with allocation codes. Both products are matched in appearance, texture, packaging, and dissolve readily in water with a mildly sweet taste, minimising the likelihood of unblinding.

### Concomitant treatments

Standard treatment for OLP, including topical corticosteroids, may be continued during the study period. Participants will be instructed to maintain their usual treatment regimen whenever clinically feasible. Any initiation, discontinuation, or dose modification of OLP-related treatments during the study period will be recorded. No dietary restrictions will be imposed, but participants will be instructed to maintain their usual dietary habits and to avoid initiating new probiotic, prebiotic, or fibre supplements other than the assigned study product. The use of inulin-containing supplements will be prohibited. Adherence will be monitored using the daily dietary record, in which participants will record whether they consumed the assigned study product each day.

### Participant timeline

The schedule of enrolment, allocation, interventions, and assessments is shown in Fig 1.

**Fig 1 pone.0356180.g001:**
[figure not shown]
SPIRIT schedule of enrolment, allocation, interventions, and assessments.

This figure summarises the timing of participant enrolment, randomisation, intervention, dietary assessment, biospecimen collection, clinical assessments, and adverse event monitoring during the trial.

### Outcomes

#### Primary outcome.

The primary outcome is the change from baseline to Week 6 in the summed relative abundance of prespecified butyrate‑producing taxa, including *Faecalibacterium prausnitzii*, *Anaerostipes hadrus*, the *Eubacterium hallii* group (including *Anaerobutyricum* spp.), *Agathobacter rectalis*, and *Fusicatenibacter saccharivorans*. These taxa were selected based on their established role in colonic butyrate production and their depletion in patients with OLP in our previous study [6].

#### Secondary outcomes.

Secondary outcomes include changes in gut and salivary microbiota composition and diversity, faecal short-chain fatty acid concentrations, peripheral blood Treg counts, blood test parameters (white blood cell count, eosinophil count, and serum IgE), and clinical symptoms of OLP. Clinical severity will be assessed using the Oral Lichen Planus Disease Activity Score (OLP-DAS) [12]. These outcomes are intended to capture the broader biological and clinical effects of inulin supplementation beyond the prespecified primary taxa.

#### Exploratory outcomes.

Exploratory outcomes will include additional analyses aimed at generating mechanistic insights into the effects of inulin supplementation. These will comprise changes in other butyrate‑producing taxa not included in the primary outcome, extended profiling of faecal short‑chain fatty acids, exploratory correlations between gut microbiota composition and peripheral blood Treg counts, phenotypic characterisation of Treg subsets, and post‑hoc responder versus non‑responder analyses. Dietary assessment during the intervention period will be conducted using a daily dietary record to monitor short-term changes in eating behaviour that may influence microbiota or clinical responses. A copy of the daily dietary record is provided as S3 File. Details of these outcomes, including assessment methods and time points, are summarised in Table 1.

**Table 1 pone.0356180.t001:** Primary, secondary, and exploratory outcomes, including assessment methods and time points.

Outcome category	Outcome	Method	Time points
Primary	Change in the summed relative abundance of prespecified butyrate-producing taxa*	16S rRNA gene sequencing; QIIME 2 pipeline	Weeks 2 (baseline), 6 (end of intervention), and 10 (follow-up)
Secondary	Gut microbiota composition	16S rRNA gene sequencing of faecal samples; QIIME 2 pipeline	Weeks 2, 6, and 10
	Gut microbiota diversity	Alpha-diversity (Shannon, Simpson, Faith's PD) and beta-diversity (Bray-Curtis, UniFrac)	Weeks 2, 6, and 10
	Faecal organic acid concentrations (SCFAs)	HPLC-MS/MS or GC for butyrate, acetate, and propionate	Weeks 2 and 6
	Salivary microbiota composition	16S rRNA sequencing of saliva samples; QIIME 2 pipeline	Weeks 2, 6, and 10
	Blood test parameters	Automated haematology and biochemistry analyser	Weeks 2 and 6
	Peripheral blood Treg counts	Flow cytometry (CD4 + CD25 + Foxp3+); standardised gating strategy (lymphocytes - > singlets - > CD3 + CD4 + - > CD25 + Foxp3+); central analysis at Kyushu University	Weeks 2 and 6
	Clinical symptoms of OLP	Oral Lichen Planus Disease Activity Score (OLP-DAS)	Weeks 2, 6, and 10
Exploratory	Additional butyrate-producing taxa	16S rRNA sequencing; genus- and species-level profiling	Weeks 2, 6, and 10
	Extended SCFA profiling	HPLC-MS/MS or gas chromatography	Weeks 2 and 6
	Microbiome-immune correlations	Integrated analysis of microbiota and Treg data	Weeks 2 and 6
	Treg phenotypic subsets	Extended flow cytometry markers (e.g., CD45RA + /-, Helios + /-)	Weeks 2 and 6
	Responder versus non-responder analysis	Unsupervised clustering integrating microbiome, immune, and clinical parameters	Post hoc
	Dietary intake during intervention	Daily dietary record	Week 2–6

*Prespecified taxa include *Faecalibacterium prausnitzii*, *Anaerostipes hadrus*, the *Eubacterium hallii* group (including *Anaerobutyricum* spp.), *Agathobacter rectalis*, and *Fusicatenibacter saccharivorans*.

### Sample size calculation

In our previous cross-sectional study, the mean relative abundance of butyrate-producing bacteria was approximately 12.4% (SD 8.1%) in patients with OLP and 14.7% (SD 8.2%) in healthy controls. Prior randomised trials in healthy adults have reported that inulin or inulin-type fructan supplementation at comparable doses can increase the relative abundance of fermentative taxa by approximately 5–15 percentage points, with concurrent increases in faecal short-chain fatty acid concentrations. On the basis of these data, we assumed that inulin supplementation would increase the summed relative abundance of the five prespecified butyrate-producing taxa by 12.5 percentage points from baseline, compared with 2.5 percentage points in the placebo group, yielding an expected between-group difference of 10 percentage points.

Because no prior intervention study has examined this response in patients with OLP, a conservative common standard deviation of 15% was adopted to account for expected variability in this patient population. Based on a two-sample comparison of the primary outcome between groups, assuming a two-sided significance level of 0.05, 80% power, and a standardised effect size of approximately 0.67, approximately 36 participants per group are required. Allowing for approximately 10% dropout, the target sample size was set at 40 participants per group, for a total of 80 participants. The calculation was performed using G*Power version 3.1.9.

### Statistical analysis

All analyses will follow the intention-to-treat principle. Statistical tests will be two-sided with a significance level of 0.05 unless otherwise specified. Analyses will be performed using R (version 4.3.1 or later).

The primary outcome is the change from baseline to Week 6 in the combined relative abundance of five prespecified butyrate-producing taxa. The between-group difference will be assessed using a two-sample t-test or Mann–Whitney U test depending on distributional assumptions. ANCOVA adjusting for baseline values will be performed as a prespecified supplementary analysis. Because 16S rRNA gene sequencing data are compositional, a sensitivity analysis of the primary outcome using centred log-ratio transformation will be performed.

Secondary continuous outcomes will be analysed using ANCOVA models adjusting for baseline values. Repeated measures will be analysed using linear mixed-effects models with random intercepts to account for within-participant correlations and to evaluate time-by-group interactions.

Microbiome sequencing data will be processed using the QIIME 2 [13,14] platform. Taxonomic assignment will be performed using a prespecified reference database and classifier. Because species-level classification by 16S rRNA gene sequencing may be limited for some taxa, the primary analysis will use the most resolved taxonomic level that can be reliably assigned by the sequencing region and classifier. Taxa corresponding to the prespecified butyrate-producing bacteria will be aggregated according to a predefined taxonomic mapping before unblinding. Alpha diversity indices will be compared using parametric or non-parametric tests as appropriate. Beta diversity will be analysed using PERMANOVA based on UniFrac and Bray–Curtis distance matrices. Differential abundance analysis will be performed using LEfSe [15], with ANCOM-BC and/or ALDEx2 used as complementary approaches to account for the compositional nature of microbiome data. For multiple related comparisons, particularly microbiome taxa analyses, short-chain fatty acid comparisons, and immunological marker panels, false discovery rate correction using the Benjamini-Hochberg procedure will be applied. Adjusted p values will be reported alongside unadjusted p values where applicable.

Exploratory analyses, including changes in individual taxa, microbiome-immune correlations, Treg phenotypic subset analyses, and responder versus non-responder comparisons, will be considered hypothesis generating. Dietary intake data from the daily dietary record will be summarised descriptively.

The primary analysis will include all randomised participants with available baseline and Week 6 primary outcome data, according to the intention-to-treat principle. Missing outcome data will be examined for patterns and likely mechanisms. If missingness is judged to be at random, multiple imputation using chained equations will be performed as a sensitivity analysis. Adverse events will be summarised descriptively by treatment group. No interim analyses are planned.

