### Randomization

A stratified permuted block randomisation sequence will be generated before the start of enrolment by an independent allocation manager who is not involved in participant recruitment, treatment, or outcome assessment. Randomisation will be stratified by study site (Kyushu University Hospital and Okayama University Hospital) using variable block sizes to minimise the predictability of allocation. The allocation table for 80 participants will be generated using computer-based randomisation software and stored securely by the allocation manager.

After written informed consent is obtained and eligibility is confirmed, the enrolling investigator will contact the allocation manager to request the treatment assignment for the participant. The allocation manager will assign the participant to the next available allocation in the pre-generated sequence. At the time of each allocation, the allocation manager will record the registration date, date of consent, participant identification code, and the name of the enrolling investigator in a separate allocation log. The enrolling investigator will have no access to the allocation table or to future assignments, thereby ensuring adequate allocation concealment.

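### The primary analysis is left open between a t-test and a Mann–Whitney test on unadjusted change scores; one ANCOVA with baseline and site would fix the target quantity and gain some precision

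*Protocol article*

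**What the plan says.** All quotes are from the protocol article. The Statistical analysis section defines the endpoint as a change score: "The primary outcome is the change from baseline to Week 6 in the combined relative abundance of five prespecified butyrate-producing taxa". The test is then given as an alternative: "The between-group difference will be assessed using a two-sample t-test or Mann–Whitney U test depending on distributional assumptions". No normality criterion, threshold or default test follows.

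For the same endpoint, "ANCOVA adjusting for baseline values will be performed as a prespecified supplementary analysis". For the other continuous endpoints, "Secondary continuous outcomes will be analysed using ANCOVA models adjusting for baseline values".

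The Randomization section says: "Randomisation will be stratified by study site (Kyushu University Hospital and Okayama University Hospital) using variable block sizes". No model or test in the Statistical analysis section mentions site, and neither primary test as named can take a covariate.

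The Sample size calculation section assumes a between-group difference of 10 percentage points (12.5 against 2.5) and a common SD of 15%, and concludes: "80% power, and a standardised effect size of approximately 0.67, approximately 36 participants per group are required". With about 10% dropout this becomes 40 per group. The section does not say whether 15% is the SD of the change or of a single visit. The only SD it reports for patients is 8.1%, from a cross-sectional study.

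Under Blinding, analysts see coded groups until the primary analysis is completed and locked.

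**The concern.** **The quantity estimated is not fixed.** A t-test addresses the difference in mean change, in percentage points. A Mann–Whitney test addresses the rank ordering of changes. The distribution of changes can be judged only from trial data, so the data decide which of the two the primary result reports. Only the first corresponds to the 10-point difference behind the sample size. The choice is likely to arise in practice. With a mean of 12.4% and SD of 8.1%, a normal distribution would put about 6% of patients below zero (12.4/8.1 = 1.53 SDs), so the raw abundances are probably skewed.

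**The primary endpoint gets the less efficient method.** Baseline adjustment is used for secondary outcomes and is already planned as a supplement for the primary one, yet the headline result forgoes it.

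**The stratification factor is unused.** If change differs by site, an analysis that ignores site has a standard error that is somewhat too large.

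At stake are an unambiguous primary result and some precision, in a trial that expects to enrol only 26–28 patients a year (Trial status).

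**Working it through.** **1. The plan's own figure.** Inputs from Sample size calculation: difference 10, SD 15, two-sided alpha 0.05, power 80%. The normal approximation gives 36 per group. With the noncentral t, power at 36 per group is 80.05% for d = 0.67 and 79.7% for d = 10/15. Allowing for dropout, 36/0.90 = 40 per group, 80 in total. The stated figures reproduce.

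**2. ANCOVA with equal SDs at both visits.** Let r be the correlation between baseline and Week 6 (not given; assumed 0.3 to 0.9).
- Change-score variance: 2s²(1 − r). ANCOVA residual variance: s²(1 − r²). Ratio: (1 + r)/2.
- Read 15 as the SD of the change, so d becomes (10/15)/√[(1 + r)/2], with 36 per group:

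| r | Variance ratio | Power | Visit SD implied by change SD 15 |
|---|---|---|---|
| 0.3 | 0.65 | 93.3% | 12.7 |
| 0.5 | 0.75 | 89.6% | 15.0 |
| 0.7 | 0.85 | 85.6% | 19.4 |
| 0.9 | 0.95 | 81.6% | 33.5 |

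The last column is 15/√[2(1 − r)]. Every value exceeds the only patient SD reported, 8.1.

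**3. ANCOVA with baseline SD 8.1 and change SD 15.** Let b be the slope of Week 6 on baseline (not given; assumed). The proportional variance reduction is (1 − b)² × 8.1²/15².
- b = 0.3: 0.49 × 65.61/225 = 14%; power 85%.
- b = 0.5: 0.25 × 65.61/225 = 7%; power 83%.
- b = 0.7: 0.09 × 65.61/225 = 3%; power 81%.

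The extreme b = 0 gives 29% and 91%.

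**4. If 15 is the SD at each visit.** Power for change score against ANCOVA is 65% against 83% (r = 0.3), 80% against 90% (r = 0.5) and 95% against 97% (r = 0.7).

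**5. Choosing between the two tests.** Simulation with 36 per group, 10,000 null data sets per distribution, and a Shapiro–Wilk test on residuals as the assumed rule:

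| Distribution | Type I error, fixed rule | Type I error, smaller p-value taken |
|---|---|---|
| Normal | 0.050 | 0.058 |
| t, 3 df | 0.052 | 0.065 |
| Skewed (lognormal) | 0.048 | 0.067 |

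**6. Leaving out site.** Simulation with 72 patients, an assumed 54/18 split balanced within site, and a site effect on the change:

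| Site effect (points) | Type I error, unadjusted | Power, unadjusted | Power, adjusted |
|---|---|---|---|
| 5 | 0.047 | 79.5% | 80.2% |
| 10 | 0.042 | 77.3% | 79.6% |
| 15 | 0.033 | 73.4% | 78.8% |

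**The case against.** The planned comparison is a valid randomised comparison and is the one the trial was sized for. It is unbiased under randomisation, and the supplementary ANCOVA already shows the effect of any chance baseline imbalance. This stands. A reader might infer that the plan is biased, or that it loses power it promised; the documents support neither.

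A reader might also infer a materially inflated error rate, or several competing primary p-values. Under a fixed rule the error rate stays near 5%. It reaches 6–7% only if the smaller p-value is always taken, and coded groups make that selection less useful, though both p-values would still be visible. The ANCOVA is labelled supplementary and the log-ratio analysis a sensitivity analysis, so the only open choice is between the two named tests.

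A rank test can also be the more powerful choice. In the same simulations, with a pure shift of 10 points, it had about 95% power for heavy-tailed and skewed data, against 83% and 79% for the t-test; for normal data it had 78% against 80%. That is a good reason to report it, but it does not make the rank comparison an estimate of the 10-point mean difference.

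A change score already removes stable differences in level between sites. A clear loss from omitting site needs an effect on the change of about 15 points, more than the 12.5 points assumed for inulin itself.

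Finally, a selection rule or a covariate list could stand in the full protocol or a separate analysis plan, neither of which is shown. That would not settle the point, because this text itself gives the unadjusted test the primary role and ANCOVA the supplementary one.

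**Conclusion.** The point holds as a should-fix. The text does not fix which quantity the primary result estimates, while the sample size rests on a mean difference. It also withholds from the primary endpoint an adjustment that it applies to secondary ones, and it uses the stratification factor nowhere.

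The efficiency gain is real in expectation but uncertain in size. Against about 80% now, with change SD 15 and 36 per arm, it is roughly 2 to 13 points of power under equal visit SDs (r from 0.9 down to 0.3). It is roughly 1 to 6 points with baseline SD 8.1 (slope from 0.7 down to 0.3). A reader might take the upper figures, around 90% or more, as the expected gain. The documents do not support that, because those figures need visit SDs well above the one reported. Omitting site is at most conservative.

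**What to change.** State one primary analysis: ANCOVA of the Week 6 combined abundance (or the change) on treatment, baseline abundance and site, reporting the adjusted mean difference with a 95% CI. Fix one inference method in advance for all cases, for example HC3 standard errors whatever the residuals look like; making it depend on observed skewness would bring back a data-dependent choice. Relabel the unadjusted t-test and the Mann–Whitney test as sensitivity analyses, and keep the planned log-ratio analysis. The target of 80 participants need not change under the stated assumptions.

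No new data are needed, since baseline and site are already recorded. The cost is a wording change that, under Ethical considerations, needs ethics committee approval before implementation and a registry update. Recruitment has begun, but Trial status reports that no outcome had been analysed at submission, so the change is still credible if it is made before any outcome analysis.

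### The ANCOVA for secondary outcomes states no scale for serum IgE, eosinophils and SCFAs and omits site; if these markers are right-skewed, a literal raw-scale reading loses efficiency but stays valid

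*Protocol article*

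**What the plan says.** All references are to the protocol article.

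- **Model (Statistical analysis):** "Secondary continuous outcomes will be analysed using ANCOVA models adjusting for baseline values". No scale, transformation or fallback is given, and baseline is the only covariate named. Repeated measures go to linear mixed models.
- **Outcomes covered:** Secondary outcomes lists "blood test parameters (white blood cell count, eosinophil count, and serum IgE", together with SCFAs, Treg counts and OLP-DAS. For the SCFAs, Table 1 gives "HPLC-MS/MS or GC for butyrate, acetate, and propionate". Table 1 schedules SCFAs, blood parameters and Tregs at Weeks 2 and 6 only. With a single post-baseline value, baseline-adjusted ANCOVA is naturally their main analysis.
- **Provision for shape elsewhere in the same section:** the primary outcome has a choice between a t-test and a Mann–Whitney test, plus a centred log-ratio sensitivity analysis. Alpha diversity has a choice between parametric and non-parametric tests.
- **Error rate:** "Statistical tests will be two-sided with a significance level of 0.05 unless otherwise specified". SCFA comparisons and immunological panels also receive Benjamini–Hochberg correction.
- **Site (Randomization):** allocation is stratified by the two hospitals.

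**The concern.** Concentrations and cell counts cannot be negative and may have a long right tail. On the raw scale a few high values then dominate both the residual variance and the fitted baseline slope, so the baseline adjustment removes less noise than it could. The SCFAs and immune markers are the link between a shift in taxa and the immune mechanism set out in the Introduction, so a needless loss of precision there weakens the interpretation of the primary result.

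The article considers distribution for the primary outcome and alpha diversity, but not for the concentrations and counts, where skew is at least as plausible. If the sentence is read as leaving the scale open, the choice could be made after the data are seen. Either reading is settled by the same short addition. Site is a separate and smaller matter: it was used to stratify the randomisation but does not appear in the analysis model.

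**Working it through.** **1. The plan's own figure.** Sample size calculation gives "yielding an expected between-group difference of 10 percentage points" and "a conservative common standard deviation of 15% was adopted", with "assuming a two-sided significance level of 0.05, 80% power, and a standardised effect size of approximately 0.67".

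n per group = 2 × (1.960 + 0.842)² × (15/10)² = 2 × 7.85 × 2.25 = 35.3, rounded up to 36. This agrees with "approximately 36 participants per group are required". The noncentral t distribution with d = 0.67 and 36 per group gives power 0.8005, and 36/0.90 = 40 per group. The figure reproduces, but it concerns the primary outcome only. The article states no power, SD or effect for serum IgE, eosinophils or SCFAs.

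**2. Set-up for the skewed markers.**

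- From the article: 36 per group, 1:1 allocation, two-sided 0.05, baseline adjustment.
- Assumed, because the article is silent: log-normal values, a multiplicative effect, log-SD σ from 0.3 to 2.0, and log-scale baseline correlation ρ from 0.5 to 0.9.
- The effect is chosen so that log-scale ANCOVA (72 − 3 = 69 residual df) has about 80% power: log effect = 0.67 × σ × √(1 − ρ²). For example, σ = 1.0 and ρ = 0.7 give 0.67 × 0.714 = 0.478, a ratio of exp(0.478) = 1.61.
- Each cell has 10,000 simulated trials. The same data are analysed twice: log values on log baseline, and raw values on raw baseline.

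**3. Power of raw-scale ANCOVA** (log-scale power 79–80% in every cell)

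| Assumed log-SD | ρ = 0.5 | ρ = 0.7 | ρ = 0.9 | Share of power lost |
|---|---|---|---|---|
| 0.3 | 77.5% | 77.2% | 76.2% | 3–4% |
| 0.5 | 72.5% | 72.6% | 70.6% | 8–11% |
| 0.7 | 67.4% | 65.9% | 63.3% | 16–20% |
| 1.0 | 56.4% | 54.0% | 49.8% | 29–38% |
| 1.5 | 38.0% | 34.0% | 31.1% | 52–61% |
| 2.0 | 24.6% | 22.2% | 20.3% | 69–74% |

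With 40 per group the results are nearly the same.

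**4. Type I error.** With no effect, raw-scale ANCOVA rejected in 2.5% to 5.6% of trials at 36 per group. The highest cell, 5.6%, came from data in which the log-scale test, exact there, rejected in 5.7%, so it is simulation noise. At large log-SD the raw-scale test is conservative.

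**5. Dependence on a multiplicative effect.** The run was repeated with log-normal data and an additive shift of 0.67 raw residual SDs, for log-SD 0.5 to 1.5 and ρ of 0.5 and 0.7. Raw-scale power was 80–91% and log-scale power 95–100%. With log-normal data, the advantage of logs is therefore not produced only by assuming a ratio effect.

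**6. An illustration from the article.** The only related spread given is butyrate-producer abundance in OLP: mean 12.4%, SD 8.1%. The CV is 8.1/12.4 = 0.65, and under log-normality the log-SD is √ln(1 + 0.65²) ≈ 0.6. If SCFAs varied similarly, which is an assumption, raw-scale power would lie between the 0.5 and 0.7 rows, at about 63–73%.

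**7. Site.** Adding it costs one degree of freedom (72 − 4 = 68 instead of 69). The article gives no between-site difference, so no gain is calculated.

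**The case against.** The strongest objection is that the article does not say raw scale. ANCOVA of log values on log baseline would satisfy the sentence equally well, and the scale for individual laboratory markers is a detail commonly left to the full protocol (S2 File) or an SAP, neither of which is shown. This stands: raw scale is only the literal reading, and if either document sets the scale the point is closed. What remains is that the article does fix a model and a covariate for these outcomes, and does provide for shape in other outcomes in the same section.

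Second, the premise of skew comes from outside the article, and exactly log-normal data favour the log-scale model by construction. This stands in part. The additive run shows that the form of the effect is not decisive, but milder departures from log-normality were not tested. With little skew the choice hardly matters, as the 0.3 row shows.

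Third, these are secondary outcomes without a power target, and many of the p values are FDR-adjusted, so power at nominal 0.05 is only indicative. This also stands, and it keeps the point minor.

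A reader might also infer that Treg counts need logs. Nothing in the article describes their distribution, and that case is not made here.

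**Conclusion.** The point holds as a minor improvement to efficiency and clarity. It is not an error or a contradiction in the article. Taken literally, the rule is raw-scale ANCOVA without the stratification factor. If serum IgE, eosinophils and SCFAs are right-skewed, that analysis remains valid but is less efficient, by an amount that depends on a spread the article does not give: about 2 to 4 percentage points of power at a log-SD of 0.3, and more than 40 at 1.5.

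Two stronger readings are tempting and not supported. One is that the plan stands to lose up to half its power on these outcomes. A fall from 80% to 40% needs an assumed log-SD of about 1.25 to 1.45. Half is neither a typical value nor an upper bound, and no single figure covers three differently distributed markers. The other is that skew would produce false positives; the simulation shows type I error at or below nominal, within simulation error.

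The figures rest on log-normal data, a multiplicative effect, 36 per arm and baseline correlations of 0.5 to 0.9.

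**What to change.** Before unblinding, state the following:

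- Serum IgE, eosinophil count and each SCFA are analysed by ANCOVA on log values, adjusted for log baseline and site, and reported as geometric mean ratios with 95% CIs.
- Zeros and values below detection are handled by a prespecified rule, with any offset fixed in advance.
- The ANCOVA for the other secondary continuous outcomes, including white cell count and Treg counts, also includes site. No log scale is requested for these.

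The cost is two or three sentences and one degree of freedom. Under Ethical considerations, changes to statistical analyses go to the ethics committee and the registry. Trial status reports that recruitment is ongoing and that no outcome analyses have been performed, so there is time. The downsides are small: effects appear as ratios instead of differences in means, and results may depend somewhat on the offset used for zeros. If the full protocol or an SAP already contains this, no change is needed beyond a cross-reference.

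### Alpha diversity is given two incompatible analysis rules, and differential abundance is led by LEfSe, which has no baseline term and works on relative abundances

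*Protocol article*

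**What the plan says.** The Secondary outcomes section defines these outcomes as changes: "Secondary outcomes include changes in gut and salivary microbiota composition and diversity". Table 1 lists Shannon, Simpson and Faith's PD as the alpha-diversity indices, with gut samples at Weeks 2, 6 and 10.

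The Statistical analysis section first sets a general rule: "Secondary continuous outcomes will be analysed using ANCOVA models adjusting for baseline values". It adds random-intercept mixed models for repeated measures. Two paragraphs later it gives the indices a sentence of their own: "Alpha diversity indices will be compared using parametric or non-parametric tests as appropriate". That sentence names no baseline term, time point or change score.

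On taxa, the same section says: "Differential abundance analysis will be performed using LEfSe". ANCOM-BC and/or ALDEx2 are added as complementary methods, expressly because the data are compositional. For the same reason the primary outcome has a centred log-ratio sensitivity analysis. Benjamini-Hochberg correction is required for taxa analyses, and changes in individual taxa are classed as hypothesis generating.

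**The concern.** There are two separate defects.

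First, alpha diversity is continuous, secondary and measured three times, so the general rule already covers it. Its own sentence then points to a different kind of analysis and leaves the type of test open. Both cannot be the main analysis, and the text does not say which prevails. At stake is precision, together with a choice of model for a secondary outcome that could be made after the data are seen.

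Second, LEfSe screens taxa with rank tests between groups and orders them by a linear discriminant score, both on relative abundances. It has no baseline covariate and no within-participant term, so it does not by itself estimate the changes that define the secondary outcomes. The plan assigns the compositional problem to other methods, but makes those methods secondary and does not fix which will be used. If inulin raises the target taxa as assumed, the remaining taxa must fall as a share of the total, and the lead method could present that fall as depletion.

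**Working it through.** **Inputs.** From Sample size calculation: mean abundance 12.4% in patients with oral lichen planus; assumed increases of 12.5 (inulin) and 2.5 (placebo) percentage points; "a conservative common standard deviation of 15% was adopted"; 36 per group before dropout. From Statistical analysis: two-sided 0.05. The baseline-to-Week-6 correlation, rho, is not given and is varied from 0.3 to 0.8.

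**The plan's own figure.** The difference is 12.5 − 2.5 = 10 and d = 10/15 = 0.67. The plan states "80% power, and a standardised effect size of approximately 0.67, approximately 36 participants per group are required". The normal approximation gives 36 per arm. The exact t-test gives 36.3 at d = 0.6667 and 35.96 at d = 0.67. Allowing for dropout, 36/0.9 = 40. The figure reproduces and is not in dispute.

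**Alpha diversity: precision.** Set the SD to 1 at both time points. The variances are then:
- Week 6-only test: 1
- change-score test: 2(1 − rho)
- ANCOVA: 1 − rho²

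ANCOVA relative to Week 6 only is therefore 1 − rho². Relative to change scores it is (1 − rho²)/[2(1 − rho)] = (1 + rho)/2. The N each test needs, relative to ANCOVA, is the inverse of these ratios.

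| rho | Change-score variance | ANCOVA variance | ANCOVA / change | N, Week 6 only vs ANCOVA | N, change vs ANCOVA |
|---|---|---|---|---|---|
| 0.3 | 1.40 | 0.91 | 0.65 | 1.10 | 1.54 |
| 0.5 | 1.00 | 0.75 | 0.75 | 1.33 | 1.33 |
| 0.7 | 0.60 | 0.51 | 0.85 | 1.96 | 1.18 |
| 0.8 | 0.40 | 0.36 | 0.90 | 2.78 | 1.11 |

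For illustration, take 36 per arm and an assumed true difference of 0.5 SD. Power at rho 0.3 / 0.5 / 0.7 / 0.8 is:
- Week 6 only: 55% throughout
- change scores: 42% / 55% / 77% / 91%
- ANCOVA: 59% / 68% / 83% / 94%

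**Differential abundance: closure.** Take 12.4% as the starting level of the target taxa in both arms.
- Target taxa at Week 6: 12.4 + 12.5 = 24.9% (inulin); 12.4 + 2.5 = 14.9% (placebo)
- All other taxa: 100 − 24.9 = 75.1%; 100 − 14.9 = 85.1%
- Ratio: 75.1/85.1 = 0.882, about 11.8% lower with inulin; log ratio −0.125

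This shift arises with no change in the absolute amounts of the other taxa. To see how often one such taxon would be flagged, apply a two-sample t-test on log relative abundance at 0.05 with 36 per arm, as a stand-in for the rank test and before any discriminant-score filter or multiplicity correction. The chance is 41% / 18% / 10% / 8% for an assumed log-scale SD of 0.3 / 0.5 / 0.8 / 1.0. Benjamini-Hochberg raises the bar for flagging, but the shift is in the quantity being tested, so the correction does not take it away.

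**The case against.** The strongest reply is that the sentences can be read together. The general rule governs, and the alpha-diversity sentence only allows a non-parametric alternative. A reader might infer that alpha diversity will be analysed without the baseline sample. The text does not say that. The outcome is defined as a change, so the test could be on change scores, which are neither stated nor excluded. What stands is that the rule is unclear and that even the change-score reading is less precise than ANCOVA.

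A reader might also infer that LEfSe results would be reported without error control. The document does not support this: Benjamini-Hochberg expressly covers taxa analyses, with adjusted p values reported. How it attaches to LEfSe is unstated, but an article may leave that to the full protocol or analysis plan.

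Nor is compositionality ignored. At least one compositional method is planned, and the primary outcome has a log-ratio sensitivity analysis. The defect is the order of the methods and the open choice between them.

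Finally, it would be wrong to say that omitting baseline turns chance imbalance into false inulin effects. Under randomisation, the unadjusted comparison keeps its nominal type I error, and the cost is precision. It is also fair that individual-taxa changes are labelled hypothesis generating and that composition is examined by PERMANOVA as well.

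**Conclusion.** The point holds in limited form. The two rules for alpha diversity need reconciling. Following the specific sentence instead of the general one would forgo a variance reduction, against a Week 6-only test, of 25% at rho 0.5 or 49% at 0.7. Against change scores the reduction forgone is 25% or 15%. These figures assume equal variances at the two visits and a correlation that the documents do not supply.

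Making LEfSe the lead method sits badly with the plan's own statement that the data are compositional. On the plan's assumed effect, non-target taxa would look about 11.8% lower on average from closure alone. That figure assumes that 12.4%, reported for butyrate producers in the earlier cross-sectional study, applies to the five target taxa in both arms. The lower share is real as a share; the error would be to read it as depletion.

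The consequences stay within secondary and hypothesis-generating results. The primary outcome and the sample size of 80 are unaffected.

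**What to change.** 1. Replace the alpha-diversity sentence with the existing rule: baseline-adjusted ANCOVA for each index at Week 6, and the mixed model across Weeks 2, 6 and 10. Add site to both, since randomisation is stratified by it.
2. Name one compositional, covariate-capable method as the main differential-abundance analysis. An example is ANCOM-BC with treatment, site, and either baseline or time-by-group terms. If several samples per participant enter the model, the chosen form must account for that. Apply Benjamini-Hochberg to the p values of this method.
3. Keep LEfSe as a descriptive display only.

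The cost is minor scripting and probably fewer taxa flagged. The methods are already named in the plan and the Week 2 samples are already scheduled. The Trial status section says that no outcome analyses have been performed, so the change can still be prespecified through the amendment route in Ethical considerations.
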